# Effects of prebiotic supplement on gut microbiota, drug bioavailability, and adverse effects in patients with colorectal cancer at different primary tumor locations receiving chemotherapy: study protocol for a randomized clinical trial

**DOI:** 10.1186/s13063-023-07137-y

**Published:** 2023-04-12

**Keywords:** Colorectal cancer, Primary tumor locations, Gut microbiota, Adverse effects, Drug bioavailability, Prebiotic

## Abstract

**Background:**

The prevalence of colorectal cancer (CRC) worldwide is a huge challenge to human health. Primary tumor locations found to impact prognosis and response to therapy. The important role of gut microbiota in the progression and treatment of CRC has led to many attempts of alleviating chemotherapy-induced adverse effects using microecologics. However, the underlying mechanism of the difference in the prognosis of different primary tumor locations and the synergistic effect of prebiotics on chemotherapy need to be further elucidated. This study aims to explore the differences in tumor microbiota and examine the effectiveness of xylooligosaccharides (XOS) on gut microbiota, adverse effects, and bioavailability of chemotherapy drugs in CRC patients at different primary tumor locations.

**Methods:**

This is a double-blinded, randomized, parallel controlled clinical trial. Participants with left-sided CRC (LSCRC, *n* = 50) and right-sided CC (RSCC, *n* = 50) will randomly allocated to prebiotic group (*n* = 25) or control group (*n* = 25) and will receive either a daily XOS (3 g/day) or placebo, respectively, for 12 weeks. The primary outcomes will be the differences in the mucosa microbiota composition at different tumor locations and differences in gut microbiota composition, adverse effects, and blood concentration of capecitabine posttreatment. The secondary outcomes will include other blood indicators, short-chain fatty acids (SCFAs) concentration, quality of life, and mental health.

**Discussion:**

This study will reveal the potential benefits of prebiotic for improving the gut microbiota composition, alleviating the adverse effects, and improving the efficacy of chemotherapy in patients with CRC. In addition, this study will provide data on the different distribution of tumor microbiota and the different changes of gut microbiota during treatment in LSCRC and RSCC, which may provide novel insights into personalized cancer treatment strategies based on primary tumor locations and gut microbiota in the future.

**Trial registration:**

Chinese Clinical Trial Registry (www.chictr.org.cn): ChiCTR2100046237. Registered on 12 May 2021.

## Introduction

Colorectal cancer (CRC) is a common malignant tumor of the gastrointestinal tract that seriously affects the health of the digestive system. And the development of this tumor is a complex and multi-step process, from small dysplastic lesions of normal colorectal mucosa, through adenomatous polyps, to carcinoma in situ [1]. Based on location, CRC can be classified into left-sided CRC (LSCRC) and right-sided CC (RSCC). RSCC is defined as any tumor occurring in the cecum, ascending colon, hepatic flexure, or first two thirds of the transverse colon, while the LSCRC is defined as any tumor occurring in the latter one third of the transverse colon, splenic flexure, descending colon, sigmoid colon and rectum [2]. Worldwide, colorectal cancer (CRC) has become the third-ranked cancer in incidence and the second-ranked in mortality. It is estimated that 935,000 people died of CRC in 2020 according to the 2020 Global Cancer Statistics [3]. Lacking of physical activity, obesity, and diet were all independent factors related to the risk of CRC [4]. Some studies suggest that factors causing the imbalance of intestinal flora may also be significant to the carcinogenesis of CRC [5, 6]. Besides, different primary tumor locations differ in incidence, pathogenesis, clinical characteristics, survival prognosis, molecular biological characteristics, and gut microbiota [7]. Several studies have demonstrated that patients with LSCRC had a significantly better prognosis compared with those with RSCC [8–11].

Increasing evidence supports the character of intestinal flora in the pathogenesis and treatment of CRC. *Fusobacterium nucleatum* adheres, invades, and induces carcinogenic and inflammatory responses via its unique FadA adhesion to activate the growth of CRC cells [12]. Other than the direct effect of specific bacteria on partial tissues, the broader bacterial community may regulate the risk and progression of CRC via competitive rejection and other mechanisms. Gut microbiota-dependent short-chain fatty acids (SCFAs) generation fermented from dietary fiber exert protection against colorectal tumorigenesis in rodents [13].

At present, cytotoxic drugs are generally applied for postoperative adjuvant therapy or advanced CRC patients, usually accompanied by a series of adverse effects (such as constipation, diarrhea, nausea, and bone marrow suppression) and individual differences in drug efficacy [14, 15]. In recent years, with the rise of “pharmacomicrobiomics,” the significance of the intestinal flora in regulating the host response to chemotherapeutic drugs is increasingly recognized [16]. Intestinal flora can modulate the anti-tumor activity of chemotherapy drugs [17]. The killing effectiveness of 5-Fu on CRC can be enhanced by bacterial-derived urolithin A [18]. Importantly, proteobacteria can promote the deglycosylation of capecitabine [19]. Moreover, some studies have reported that probiotics/prebiotics can reduce the adverse effects of chemotherapy. *Lactobacillus casei* variety *rhamnosus* plays a preventive role in FOLFOX-related intestinal mucositis in CRC-bearing mice [20]. In CRC patients, *L. rhamnosus* GG consumption reduced the incidence of 5-FU-induced severe diarrhea and abdominal discomfort compared with guar gum fiber [21]. Lu et al. found that synbiotics (containing a variety of probiotics and prebiotic ingredients) can help relieve postoperative chemotherapy-related adverse effects, further improving the quality of life (QoL) in CRC patients [22]. Furthermore, accumulating evidence demonstrated that prebiotics, such as non-digestible oligosaccharides, can reverse chemotherapy-induced intestinal dysbiosis through selective colonization of the probiotic bacteria [23]. In Peng’s trials, compared to those who received enteral nutrition therapy alone, surgical patients supplied with prebiotics experienced shorter durations of hospital stay and had reduced levels of inflammatory cytokines [24]. Hence, targeting the gut microbiota in clinical practice to modulate the efficacy and toxicity of chemotherapeutic drugs has a promising future.

Although there have been some reports on the effects of microecologics on modulating intestinal flora and reducing adverse effects in patients with CRC during chemotherapy, they are still very limited. Through our current knowledge, using microecologics to interfere with the bioavailability of chemotherapeutic agents in a microbiota-dependent manner has not been reported, as well as differences in the intervention effect of prebiotics on the intestinal flora of CRC patients at different primary tumor locations.

Xylooligosaccharide (XOS) is a mixture of oligosaccharides consist of 2–9 xylose units connected by β-1,4-glycosidic bonds [25, 26], which can scape digestion by host enzymes in the small intestine and enter the large intestine directly, and served as major substrates for gut bacterial growth. XOS can be utilized by beneficial bacteria first in the intestine, enriching bifidobacteria and lactobacillus, and inhibiting the proliferation of harmful bacteria such as *E. coli and Salmonella enteritidis* to reduce the production of harmful substances [27, 28]. The proliferation effect of XOS on bifidobacteria is about 20 times that of other functional oligosaccharides, with higher selectivity [29]. XOS can facilitate the generation of SCFAs such as acetic acid, propionic acid, and butyric acid [30], as well as other organic acids such as lactic acid, succinate, formic acid, isobutyric acid, and isohexanoic acid [31], which play important roles in preventing various intestinal diseases. XOS was found to increase the moisture content of stool and improve constipation [32]. In addition, XOS have a strong ability to adsorb pathogens, thereby preventing diarrhea [33]. Evidence from in vitro and animal research indicates that XOS play roles in inhibiting the secretion of inflammatory cytokines and have an effect on anti-inflammatory and anti-tumor [34, 35]. Chronic toxicology studies on XOS show that it is safe and reliable with no toxicity in humans, dogs, rodents, and other animals [36–38].

## Objectives

Firstly, this study aims to explore the difference of tumor microbiota and the different gut microbiota changes during treatment between LSCRC and RSCC. Moreover, another goal of the trial is to investigate the effect of XOS on (i) increasing the bioavailability of cytotoxic drug, (ii) reducing the adverse effects of chemotherapy, and (iii) improving the QoL of CRC patients by modifying gut microbiota.

## Methods and analysis

### Study design

This study is a single-center, randomized, parallel controlled clinical trial conducted at the Affiliated Hospital of Jiangnan University in Wuxi, China. Participants with LSCRC and RSCC will receive prebiotic or placebo intervention during postoperative chemotherapy for 3 months. The study flow is shown in Fig. 1. Study procedures and data collection are shown in Table 1 based on SPIRIT (Standard Protocol Items: Recommendations for Interventional Trials) [39].

**Fig. 1 Fig1:**
[figure not shown]
Study flowchart

**Table 1 Tab1:**
[figure not shown]
SPIRIT diagram: schedule of enrollment, interventions, and assessments

*The experiment takes 12 weeks, and every cycle of chemotherapy takes 3 weeks

### Eligibility criteria

#### Inclusion criteria

Patients diagnosed with primary CRC who will be treated with XELOX chemotherapy;Patients aged 18–80 years;Patients with an Eastern Cooperative Oncology Group (ECOG) performance status score of 0 or 1, absolute number of neutrophils ≥ 1.5 × 10^9^/L, platelets ≥ 100 × 10^9^/L, serum creatinine ≤ 1.5 times upper limit of normal (ULN), total bilirubin ≤ 1.5 times ULN, aspartate transaminase/alanine transaminase ≤ 2.5 times ULN and carcinoembryonic antigen within the normal range;Patients have not received preoperative neoadjuvant radiotherapy and chemical treatment;Written informed consent.

#### Exclusion criteria

Suffer from other tumors at the same time;Patient has other digestive tract diseases except gastrointestinal tumors, such as inflammatory bowel disease, acute gastroenteritis, etc.;Those who have taken antibiotics, drugs, or food containing probiotics within 6 months;Those with active infections or those with mental illness, cardiovascular and cerebrovascular diseases, severe cardiopulmonary dysfunction, and other serious diseases that are not suitable for chemotherapy;Those who have undergone multiple courses of chemotherapy, extensive radiotherapy, advanced age, bone marrow metastasis, severe infection, adrenal insufficiency, and severe illness;Women during pregnancy;Patients who cannot receive treatment on time and cannot cooperate fully.

#### Drop out criteria

Patients who violate medication regimen in the chemotherapy treatment;Patients who receive antibiotics, probiotics or other prebiotics during the intervention;Individuals who do not take the prebiotics consistently;Individuals who suffer complications that may be caused by prebiotics;

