#### Data collection and sample handling

The overall study design is depicted in Fig. 1. Assessment of participants will be conducted at the perioperative (baseline = week 0), pre-treatment (week 3), post-treatment (week 15), and in each chemotherapy cycle. The primary outcomes will be the differences in the microbiota composition at different CRC tumor sites and differences in gut microbiota composition, adverse reactions, and blood concentration of capecitabine in patients with CRC treated for 12 weeks with XOS or placebo. The secondary outcomes will include blood indicators (hepatic and renal function, blood glucose, blood lipid, and inflammatory cytokines), SCFAs concentration, QoL, and mental health.

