#### Adverse effects

Adverse effects, including nausea, vomiting, diarrhea, leukopenia, anemia, thrombocytopenia, diarrhea, oral mucosal reaction, peripheral neuropathy, hand-foot syndrome, pigmentation, and abnormal liver function, will be assessed in each chemotherapy cycle using the Common Terminology Criteria for Adverse Events (CTCAE) version 5.0 [40]. Patients will be informed of the types of all adverse effects prior to the start of the experiment. After the beginning of the experiment and before each chemotherapy treatment, all adverse effects will be questioned and recorded from grades I to IV according to severity in the office. There is no knowledge of the possibility of any discomfort or adverse event with this supplementation. Participants are asked to inform the investigators in time if there is any adverse event that may be associated with prebiotics. These adverse events will be recorded by investigators. Protocol modifications will be communicated to the ethics committee through an official modification request, and the participants will be notified by telephone.

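### The drop-out criteria are post-randomisation events and one overlaps with a primary outcome; unless those patients stay in follow-up and analysis, the arm comparison can be biased in a direction the document does not settle

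*Protocol article*

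**What the plan says.** The section Drop out criteria has four entries:

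- "Patients who violate medication regimen in the chemotherapy treatment"
- "Patients who receive antibiotics, probiotics or other prebiotics during the intervention"
- "Individuals who do not take the prebiotics consistently"
- "Individuals who suffer complications that may be caused by prebiotics"

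The section Data collection and sample handling names as primary outcomes, besides tumour-site microbiota, "differences in gut microbiota composition, adverse reactions, and blood concentration of capecitabine in patients with CRC treated for 12 weeks with XOS or placebo". The section Adverse effects opens its list with "Adverse effects, including nausea, vomiting, diarrhea, leukopenia, anemia, thrombocytopenia". It says that before each chemotherapy treatment "all adverse effects will be questioned and recorded from grades I to IV according to severity in the office", and that events possibly linked to the supplement are recorded too.

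Post-treatment stool (Gut microbial composition) and the capecitabine level (Blood tests) are taken only at week 15. Sample size calculation starts from 20 per group and recruits 25 to allow for withdrawal.

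Randomization and blinding keeps participants and investigators blind until data analysis. Allocation concealment provides for unblinding when a patient chooses to leave early, and Sequence generation gives the boxes only an A or a B code.

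**The concern.** Each criterion is met, if at all, after randomisation, and each can be a consequence of treatment. A suspected supplement complication such as diarrhea is itself an adverse effect. A departure from the chemotherapy regimen, irregular intake of the powder, or an antibiotic course (for example after leukopenia) can follow from toxicity. If these patients leave, those who remain are selected partly on the outcome, and randomisation no longer protects the comparison.

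This is a rule of conduct and not merely a missing analysis set. A patient who is dropped and no longer followed has no week-15 stool sample and no capecitabine level, and no later analysis plan can restore them. The allowance for withdrawal in the sample size suggests that dropped patients are not expected to be evaluable. Adverse effects are also the outcome on which the sample size rests.

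**Working it through.** **The plan's own figure.** The step from 20 to 25 per group reproduces with a drop-out of 20%: 20 / (1 − 0.20) = 25. The rate is not stated; it is implied. The 20 itself cannot be reproduced, because no effect size, SD or event rate is given.

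**Formula.** Let p be the true proportion with an adverse effect in an arm and r the share of those affected patients who are removed. If only affected patients are removed and their events are lost, the observed proportion is p(1 − r) / (1 − p·r). The documents give no adverse-effect rates, so every p and r below is an assumption.

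**No true effect, p = 30% in both arms, removal in the XOS arm only**

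| Share of XOS arm removed | Observed on XOS | Observed on placebo |
|---|---|---|
| 5% | 0.25 / 0.95 = 26.3% | 30% |
| 10% | 0.20 / 0.90 = 22.2% | 30% |
| 15% | 0.15 / 0.85 = 17.6% | 30% |

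At 10% this is a spurious benefit of about 8 points. If the same 10% were removed from the placebo arm only, the figures swap and XOS looks 8 points worse. If 10% were removed from both arms, both read 22.2% and the difference is zero.

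**Type I error.** Simulation of 100,000 trials, 50 per arm (two strata of 25), p = 50% in both arms, pooled z test at two-sided 0.05:

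| Share of affected removed, placebo / XOS | Observed difference (XOS − placebo) | Type I error |
|---|---|---|
| 0 / 0 | 0 | 0.057 |
| 20% / 20% | 0 | 0.051 |
| 40% / 40% | 0 | 0.051 |
| 10% / 30% | −6.2 points | 0.091 |
| 0 / 20% (on average 5 of 50 XOS patients) | −5.6 points | 0.084 |
| 0 / 40% (on average 10 of 50 XOS patients) | −12.5 points | 0.22 |

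The 0.057 without removal reflects the discreteness of the test. The last row loses 20% of the XOS arm, the same share as the implied drop-out.

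**True effect, equal removal in both arms**

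- Benefit, 50% on placebo and 30% on XOS, 20% of affected removed: 0.40/0.90 = 44.4% and 0.24/0.94 = 25.5%, so −20.0 becomes −18.9 points.
- The same with 40% removed: 0.30/0.80 = 37.5% and 0.18/0.88 = 20.5%, so −20.0 becomes −17.0 points.
- Harm, 40% on XOS and 30% on placebo, 40% removed: 0.24/0.84 = 28.6% and 0.18/0.88 = 20.5%, so 10 becomes 8.1 points.
- Harm at higher rates, 60% and 50%: the 10 points read 10.1 (20% removed) or 9.9 (40% removed), so almost no change.

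Equal removal therefore creates no difference under the null, and in most of these examples it shrinks a real one.

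**The case against.** Four arguments on the other side carry weight.

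1. **Drop-out is not defined as exclusion from the analysis.** The analysis set may be fixed in a full protocol or SAP that is not shown, and its absence here is no fault. This stands, and it makes the point conditional. It does not cover follow-up: nothing shown says that week-15 samples are still taken from a dropped patient.

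2. **A reader might take "blood concentration of capecitabine in patients with CRC treated for 12 weeks with XOS or placebo" to define a completer population.** The document does not support that. The abstract and the Interventions section use 12 weeks as the length of the intervention, and the phrase reads naturally the same way.

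3. **A reader might infer that two of the criteria act on the XOS arm alone, because they name only prebiotics, and hence that the result is biased in favour of XOS.** This is not established. The Interventions section speaks of handing participants a box of prebiotics when it evidently means either powder, and blinded staff could not apply the rule to one arm. If XOS reduced toxicity, more placebo patients might meet the criteria, and the bias would run against XOS. For non-adherence the direction cannot be determined.

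4. **Events may already be on record.** Adverse effects are assessed every cycle, so an event before drop-out need not be lost. The illustrations assume that it is, which makes them unfavourable cases.

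Differential removal nevertheless remains possible. The wording of two criteria permits a one-arm reading. Patients who choose to leave early are unblinded while boxes carry only A or B. If study staff learned one leaver's allocation, they could infer the code for everyone, and later judgements of what the supplement may have caused would no longer be blind.

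**Conclusion.** The point holds as a conditional one. The criteria are all post-randomisation, one overlaps with the adverse-effect primary outcome, and nothing shown keeps these patients in follow-up or analysis. If they leave either, the adverse-effect, capecitabine and microbiota comparisons can be biased.

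The document determines neither the direction nor the size. Under an assumed 30% rate, removing 5% to 15% of one arm only would move that arm's rate to between 26% and 18%. Equal blinded removal leaves the null comparison unbiased, and in most of the examples it dilutes a true difference. The loss of numbers is not a further defect, because the step from 20 to 25 already allows for withdrawal.

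**What to change.** **Wording.**

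- State that meeting a drop-out criterion does not end follow-up and does not remove the patient from the analysis.
- State that the criteria apply identically to both arms, and replace the prebiotic-only wording with a term covering both powders. When the supplement is stopped is a clinical matter for the investigators, and this change does not touch it.

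**Data.**

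- Continue to collect adverse effects, questionnaires and week-15 samples from every randomised patient who still consents.
- Count complications attributed to the supplement as adverse effects.
- For patients already dropped, include the adverse effects recorded before they left.

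**Analysis.** Make the comparison of all randomised patients in their allocated arm the main analysis for the treatment outcomes. Report the adherent, antibiotic-free subset, defined in the same way for both arms, as supplementary only.

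**Cost.** Mostly text. Patients who continue chemotherapy already attend every 3 weeks; those who leave it need some extra follow-up effort. Non-adherent patients dilute the estimate somewhat. Samples never taken from patients already dropped cannot be recovered. The article gives 1 March 2023 as the end of inclusion, so the change should be made promptly and before unblinding for analysis.

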### Selection and recruitment

Posters and leaflets will be accessible in the department of gastrointestinal surgery in the hospital so that interested candidates with CRC can get in touch with investigators to participate in the screening process. In addition, according to their patient charts, inpatients who meet inclusion criteria will be inquired about their intention for recruitment in the hospital. The eligible participants will be invited for the first visit, and two trained investigators will explain the study procedures in detail to them: (1) the purpose of this study, whether there are risks and discomforts, whether it needs to be paid, whether it is completely voluntary, etc.; (2) the types of samples collected in this study and the details of the collection; (3) the personal information of the subjects, research-related measurement indicators, and physical examination information will be kept confidential. Informed consent will be voluntarily signed by individuals who agree to participate in this study. The participants will visit the hospital for postoperative chemotherapy about 3 weeks after surgery. Since the chemotherapy regimen will change with the cancer stage, only participants who receive XELOX chemotherapy (oxaliplatin + capecitabine) will continue to participate in this trial.

### Information questionnaires and physical evaluation

The personal information of the subjects will be conducted through basic information questionnaires, including body mass index, age, gender, and dietary habit. And these data were obtained in the form of an interview. Meanwhile, physical examination (height, weight, blood pressure, heart rate, etc.) is performed before the allocation.

